## Abstract

**Background:**

Advanced stage marginal zone lymphoma (MZL) is an incurable indolent B-cell lymphoma, for which a wide variety of treatments ranging from single agent rituximab to more dose intense immunochemotherapy exists. One of the major goals in this palliative setting is to develop chemotherapy-free treatments, which approach the efficacy of immunochemotherapies, but avoid chemotherapy associated toxicity in this often elderly patient population. The PI3K inhibitor copanlisib has recently shown remarkable clinical activity in refractory or relapsed indolent B–cell lymphomas, among them MZL. Based on these data, copanlisib monotherapy was granted breakthrough designation by the FDA for the treatment of adult patients with relapsed marginal zone lymphoma who have received at least two prior therapies. However, data are still limited in particular for MZL. Based on this, the COUP-1 trial aims at testing the toxicity and efficacy of copanlisib in combination with rituximab in treatment naive and relapsed MZL.

**Methods:**

COUP-1 is a prospective, multicenter, single-arm, open-label, non-randomized phase II trial of 6 cycles (28 days cycle) of copanlisib (60 mg intravenous day 1, 8, 15) and rituximab (375 mg/m^2^ intravenous day 1) in the induction phase followed by a maintenance phase of copanlisib (d1, d15 every 4 weeks for a maximum of 12 cycles) and rituximab (d1 every 8 weeks for a maximum of 12 cycles) in patients aged ≥18 years with previously untreated or relapsed MZL in need of treatment. A total of 56 patients are to be enrolled. Primary endpoint is the complete response (CR) rate determined 12 months after start of induction therapy. Secondary endpoints include the overall response (OR) rate, progression free survival (PFS), overall survival (OS), safety and patient related outcome with quality of life.

The study includes a translational bio-sampling program with the prospect to measure minimal residual disease. The study was initiated in November 2019.

**Discussion:**

The COUP-1 trial evaluates the efficacy and toxicity of the treatment of copanlisib in combination with rituximab in patients with MZL and additionally offers the chance for translational research in this heterogenous type of lymphoma.

**Trial registration:**

ClinicalTrials.gov: NCT03474744. Registration date: 03/23/2018.

**Supplementary Information:**

The online version contains supplementary material available at 10.1186/s12885-021-08464-6.

## Background

### Marginal zone lymphoma

According to the WHO classification marginal zone lymphoma (MZL) is defined as a group of indolent non-Hodgkin lymphoma that accounts for about 10% of all B-cell lymphomas. MZL is a disease that includes three histological subtypes: splenic (SMZL), nodal (NMZL) and extranodal MZL (EMZL) with the latter tumor also known as mucosa-associated lymphoid tissue (MALT) lymphoma [1]. Although these subtypes share a similar immunophenotype, clinical and molecular characteristics as well as treatment approaches are distinct.

SMZL typically presents with enlargement of the spleen and bone marrow infiltration without or minimal peripheral lymphadenopathy. In SMZL, lymphocytosis is often an incidental finding, whereas anemia and thrombocytopenia are multifactorial features in advanced-stage disease due to bone marrow infiltration, hypersplenism and/or autoimmune phenomena. Definitive diagnosis of SMZL is based on splenectomy but is often made by combining diagnostic results of peripheral blood and bone marrow examination [2].

The clinical picture of NMZL often resembles the pattern of other nodal lymphomas, such as follicular lymphoma, and is characterized by the enlargement of peripheral, abdominal, and thoracic lymph nodes and is usually non-bulky. Diagnosis requires the exclusion of extranodal manifestations and splenic involvement [3].

The most common form is extranodal marginal zone lymphoma, which can occur in a large variety of different extranodal organs. It typically shows so-called lymphoepithelial lesions with epithelial invasion by clonal B cells and has only a low tendency to disseminate. MZL is often associated with either chronic infections as a result of chronic antigenic stimulation (e.g. Helicobacter pylori in gastric MZL lymphoma) or organ-related autoimmune diseases (e.g. Sjögren’s syndrome or Hashimoto’s thyreoiditis) [4].

### Therapeutic options for marginal zone lymphoma

Due to the indolent course of disease, an initial watch and wait strategy in the asymptomatic patient can be recommended. If the patient is in need of treatment, there are basically three options including anti-infective (antibiotics, antiviral medication), local (surgery, radiotherapy) and systemic treatment approaches. However, treatment algorithms are mainly based on retrospective data or extrapolated from studies of other lymphoma subtypes. Partly, because of the heterogeneity and the relative rarity of each MZL subtype, conducting studies remain a particular challenge in this disease.

### Rituximab as a therapeutic strategy for MZL

The CD20 antigen is expressed by B-lymphocytes on the surface of pre-B to the mature germinal center B-cells and the majority of mature B-cell neoplasia.

Rituximab targets specifically with high affinity (5 × 10^− 9^ mol/L) the glycolysated transmembrane phosphoprotein CD20. Upon binding of the Fab-fragment of the antibody to the CD20 antigen the Fc-fragment mediates various immunological responses (CDC = complement-dependent cytotoxicity, ADCC = antibody dependent cell-mediated cytotoxicity, ADP = antibody dependent phagocytosis) that contribute to the effective destruction of CD20 positive B-cells and thereby is a promising target in MZL [5–9]. Apart from the immune mediated mechanisms CD20 bound rituximab can initiate direct signaling induced cell death through redistribution of CD20 to lipid rafts (membrane domains rich in cholesterol and sphingolipids) that affect cell membrane and intracellular signaling effects [10].

Rituximab monotherapy is well tolerated, safe and has a reasonable anti-lymphoma activity at least in SMZL and EMZL. According to a recently published meta-analysis, assessing the efficacy of rituximab monotherapy in MZL, best response rates are achieved in SMZL [11] (see Table 1). Rituximab efficacy can be further augmented by adding chemotherapy. The largest trial, the IELSG-19 trial, randomized patients between chlorambucil, rituximab*/*chlorambucil and rituximab single agent in patients with no prior treatment of EMZL. In this trial, overall response (OR) rate was 78.3% with 55.8% complete response (CR) and 22.5% partial response (PR) for rituximab monotherapy compared with 94.7, 78.8 and 15.9%, respectively, for rituximab*/*chlorambucil [12, 13]. However, depending on the type of selected treatment approach, immunochemotherapy can be associated with considerable morbidity (grade ≥ 3 adverse events about 80%) and mortality rate (up to 11.9%) in MZL [14, 15].

**Table 1 Tab1:** Efficacy data of rituximab monotherapy depending on MZL subtypes

MZL subtype		Number of patients	OR (%)	CR (%)
EMZL	[11]	112	73	45
	[12]	138	78	56
SMZL [11]		122	92	58
NMZL [11]		3	33	0

*MZL* marginal zone lymphoma, *EMZL* extranodal marginal zone lymphoma, *SMZL* splenic marginal zone lymphoma, *NMZL* nodal marginal zone lymphoma, *OR* overall response, *CR* complete response

### Copanlisib as a therapeutic strategy for MZL

Nowadays, in the era of targeted medicine, small molecule inhibitors of kinases involved in B-cell signaling represent a promising area of research, including phosphatidylinositol-3-kinase (PI3K). PI3Ks are a family of heterodimeric kinases consisting of a catalytic and a regulatory subunit and are divided into three classes (class I, II and III). Four of these PI3K isoforms (PI3Kα, PI3Kβ, PI3Kγ, PI3Kδ) are categorized as class I enzymes because they can use phosphatidylinositol 4,5-bisphosphonate (PIP2) to generate phosphatidylinositol 3,4,5-triphosphate (PIP3). Elevated PIP3 in cellular membranes drives several hallmarks of the cancer phenotype such as proliferation, survival, and immune regulation (Fig. 1) [16]. PI3Kα and PI3Kβ are expressed ubiquitously, whereas PI3Kγ and PI3Kδ are highly restricted to hematopoietic tissue. Copanlisib (Bay 80–6946) is a potent pan-class I PI3K inhibitor, with approximately tenfold preferential inhibition of the PI3Kα and PI3Kδ isoform [17]. In 2016, a first-in-human phase I study reported promising anti-tumor activity of copanlisib, particularly in a small cohort of patients with advanced stage pretreated follicular lymphoma [18]. In line with that, Dreyling and colleagues demonstrated remarkable efficacy and manageable toxicity in heavily pretreated patients with indolent lymphoma. The OR was 43.7% in the indolent cohort [19]. Recently, the results of the pivotal phase II CHRONOS-1 study have led to the approval of copanlisib by the FDA. In this study, 142 patients with relapsed or refractory indolent lymphoma after two or more lines of therapy were enrolled, among 23 patients with MZL. In this lymphoma subtype the OR was 70%, including 9% with a CR and 61% with a PR (see Table 2) [21].

**Fig. 1 Fig1:**
[figure not shown]
PI3K signaling pathway in physiological and malignant B-cells. PI3K activity is regulated in both a B-cell receptor (BCR) and receptor tyrosine kinase (RTK) mode. Upon RTK stimulation PI3K catalyses phosphatidylinositol 4,5-bisphosphonate (PIP2) to generate phosphatidylinositol 3,4,5-triphosphate (PIP3), resulting in recruitment of AKT (Protein kinase B) and activation of the mTOR (mechanistic target of rapamycin) pathway. On the other hand, BCR stimulation leads to the recruitment of BTK (bruton tyrosine kinase) via PIP3 with downstream activation of the MAPK (mitogen-activated protein kinase) and NFĸB (nuclear factor ‘kappa-light-chain-enhancer’ of activated B-cells) signaling pathway. Pathological triggering of both signaling pathways eventually results in increased proliferation and survival advantage of the B-cell. MZL = marginal zone lymphoma, Syk = spleen tyrosine kinase, Lyn = kinase

**Table 2 Tab2:** Selected data of copanlisib monotherapy in relapsed or refractory B-cell-lymphoma subtypes in clinical trials

Trial	Subtype of lymphoma (%)	Number of patients	OR (%)	CR (%)	summary of treatment-emergent ≥ grade 3 (%) occurring in ≥10% of the total population
Phase I [18]	FL (66.6), DLBCL (33.3)	9	78%	11%	hyperglycemia (33), hypertension (33), lung infection (22), neutropenia (11), rash (11), anemia (11)
Phase II [20]	DLBCL (100)	79	19.4	5	hyperglycemia (33), hypertension (31)
Phase II [21]	FL (73), MZL (16), SLL 8 (6), LPL/WM (4), DLBCL (1)	142	59 (overall cohort), 70 (only MZL)	12 (overall cohort), 9 (only MZL)	hyperglycemia (41), hypertension (24), lung infection (15), neutropenia (24)

*FL* follicular lymphoma, *DLBCL* diffuse large B-cell lymphoma, *MZL* marginal zone lymphoma, *SLL* small lymphocytic lymphoma, *LPL* lymphoplasmacytic lymphoma, *WM* Waldenström’s macroglobulinemia, *OR* overall response, *CR* complete response

### Study rationale

So far, there is no well-established standard treatment for patients with MZL and systemic treatment approaches range from rituximab monotherapy to more intense immunochemotherapy. The dilemma here is that data do not consistently show an advantage on patient’s outcome with dose intense treatment. Moreover, it has to be taken into account that none of the dose intense approaches are regarded as curative and that the majority of patients suffering from MZL are elderly, highlighting the need to actively pursue safe and effective therapeutic options. Thus, mild chemotherapy-free approaches are highly attractive in this disease and the feasibility of this approach has been recently shown for the BTK inhibitor ibrutinib [22]. The hypothesis of this study is that adding copanlisib to rituximab is superior to rituximab monotherapy and is approaching the efficacy of immunochemotherapy without exposing the patient to chemotherapy associated toxicity.

## Methods and study design

The COUP-1 is a multicenter, open label, single-arm phase II study. The objective of the trial is to test the efficacy and toxicity of the treatment of the combination of copanlisib and rituximab in patients with MZL in need of treatment, who have failed or are not eligible for local therapy or relapsed after local or systemic treatment. For efficacy the rate of complete remissions according to the GELA criteria for gastric MZL or to Cheson 2007 criteria for non-gastric extranodal, nodal and splenic MZL after induction therapy will be primary analysed. The trial is registered on the clinicaltrials.gov database (NCT03474744) and is conducted in accordance with the Declaration of Helsinki. The ethics committee of Ulm University approved the COUP-1 trial as leading ethics committee for all German sites. In addition, the leading Austrian ethics committee also approved the study.

### Key inclusion and exclusion criteria

Eligible patients must be aged ≥18 years, be able to provide written informed consent and must have a proven pathological diagnosis of either extranodal, nodal or splenic CD20-positive MZL, confirmed by a reference pathology center. Patients have to be in need of treatment and both treatment naïve and relapsed/refractory patients can be included. Treatment naïve patients have to be not eligible for local treatment or local treatment must have been failed in these patients. In patients with SMZL without splenic tissue available for histologic review, the diagnosis may be confirmed by the presence of splenomegaly and typical morphologic and immunophenotypic findings in the blood and bone marrow. At least one bi-dimensionally measurable lesion (≥1.5 cm) in its largest dimension by CT scan or MRI must be met. Of note, for gastric MZL, the clinical evidence of the MZL as seen by gastroendoscopy is sufficient. All patients should have adequate bone marrow function (neutrophil counts ≥0.75 × 10^9^*/L* or baseline platelet count ≥50 × 10^9^*/L* [if not due to bone marrow infiltration by the lymphoma], GFR ≥ 40 mL/min/1.73m^2^, AST and ALT ≤3 × upper limit of normal and bilirubin ≤2 mg*/*dL or 2 × upper limit of normal).

Main exclusion criteria include ECOG *≥*2, CNS lymphoma, histologic evidence of transformation to a high grade or diffuse large B-cell lymphoma as well as chronic active hepatitis B. Ongoing immunosuppressive therapy including corticosteroids (exception *<* 4 weeks administered at a dose equivalent to ≤40 mg*/*day prednisone is allowed) are not permitted. Additional exclusion criteria comprise an unstable or new-onset angina pectoris, myocardial infarction less than 6 months prior to test drug, congestive heart failure > class II, HbA1c > 8.5% and uncontrolled arterial hypertension despite optimal medical management.

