### Treatment

Patient enrollment started in November 2019. Eligible patients receive an induction phase of copanlisib and rituximab followed by a maintenance phase of each test drug (Fig. 2). The induction phase consists of six cycles (1 cycle = 28 days). Copanlisib will be administered intravenously at a fix dose of 60 mg on days 1, 8, 15 of each cycle. Rituximab will be applied intravenously at a dose of 375 mg/m^2^ only on day 1 of each cycle.

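### The neutrophil and platelet floors are joined by 'or', so one adequate count meets the marrow criterion however low the other is; probably a slip for 'and'

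*Protocol article*

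**What the plan says.** The relevant text is one sentence in the protocol article, Key inclusion and exclusion criteria. It opens with a requirement on everyone: "All patients should have adequate bone marrow function". A bracket then lists the limits:

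- neutrophils of at least 0.75 × 10⁹/L, followed by "or baseline platelet count ≥50" × 10⁹/L;
- a qualifier placed after the platelet limit, "if not due to bone marrow infiltration by the lymphoma";
- GFR of at least 40 mL/min/1.73 m²;
- AST and ALT no more than 3 times the "upper limit of normal and bilirubin" no more than 2 mg/dL or 2 times the upper limit of normal.

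None of the exclusion criteria in the same section concerns a low neutrophil or platelet count, and no other section of the article gives a floor for either.

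**The concern.** An inclusion rule written as 'A or B' is met when either part is met. Applied literally, the criterion stops testing the second count once the first is adequate. That does not serve the stated aim of adequate marrow function in all patients.

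The stake is patient safety at entry. Low platelets from causes other than infiltration are foreseeable here: for splenic disease, the Marginal zone lymphoma section says that anemia and "thrombocytopenia are multifactorial features in advanced-stage disease due to bone marrow infiltration, hypersplenism and/or autoimmune phenomena". Infiltration is exempted by design, but hypersplenism and autoimmune disease are not. That passage says nothing about neutropenia. For neutrophils, the relevance comes from the drug: Table 2 reports grade 3 or higher neutropenia in 24% of the 142 patients in the phase II study of copanlisib monotherapy in indolent lymphoma. That figure shows why a neutrophil floor is wanted. It does not measure the extra risk from entering with a low count.

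**Working it through.** The article gives no figure to reproduce, so the check is one of logic and of how the sentence is built.

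**Step 1: read the rule as a logical statement.** Let N mean neutrophils ≥ 0.75 × 10⁹/L and P mean platelets ≥ 50 × 10⁹/L. Suppose first that infiltration is not the cause of any low count.

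| Neutrophils | Platelets | Printed rule (N or P) | Both required (N and P) |
|---|---|---|---|
| adequate | adequate | pass | pass |
| adequate | low | pass | fail |
| low | adequate | pass | fail |
| low | low | fail | fail |

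'Or' admits 3 of 4 combinations and 'and' admits 1 of 4. The 3 − 1 = 2 that differ are those with exactly one count below its limit. These are logical cases, not proportions of patients.

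**Step 2: put values in (× 10⁹/L, no infiltration).**

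- Neutrophils 1.5, platelets 10: 1.5 ≥ 0.75 is true and 10 ≥ 50 is false. 'Or' passes, 'and' fails.
- Neutrophils 0.2, platelets 60: 0.2 ≥ 0.75 is false and 60 ≥ 50 is true. 'Or' passes, 'and' fails.

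**Step 3: compare the other connectives in the bracket.** GFR, the transaminases and bilirubin are separated by commas or 'and', and AST is joined to ALT by 'and'; all of these are cumulative. The one other 'or' gives two ways of stating a single bilirubin limit (2 mg/dL, or 2 times the upper limit of normal). Only between neutrophils and platelets does 'or' turn two different tests into alternatives.

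**Step 4: ask what the infiltration exemption does under each reading.** Under 'or', a patient with one adequate count passes already, so the exemption can matter only when both counts are low. Under 'and', it rescues a patient who would otherwise fail on a lymphoma-related low count, which is the ordinary work of an exemption. Waiving the limit for infiltration also implies that low counts from other causes were meant to exclude. The text does not settle whether the exemption covers platelets only or both counts, but this step does not depend on the answer.

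**Step 5: look for a second floor.** The article has none, so nothing elsewhere in it repairs the literal reading.

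**The case against.** The strongest reply is that this is a journal article summarising key criteria. Sites enrol from the full protocol and its eligibility documents, which are not shown and may require both counts. The sentence is visibly compressed: its bracket on marrow function also holds renal and hepatic limits, so its grammar is weak evidence of the operative rule. A sensible investigator, told that marrow function must be adequate, would hardly enrol a patient with platelets of 10 × 10⁹/L and no infiltration. Even as printed, patients with both counts low are still excluded. The platelet argument concerns splenic disease, about 20% of cases by the article's own subtype split, and within that only low counts not due to infiltration. Haematology is monitored, and the safety committee reviews data after the first 6 patients and again when the 28th and the last patient have ended induction. Finally, 'or' may have been chosen to admit hypersplenic or autoimmune cases.

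Much of this stands as a limit on weight. The harm is conditional on the wording being applied, the number of patients is unknown, and safety monitoring softens the consequence. It does not remove the defect. Condensing excuses leaving something out, but here a numeric criterion is stated and gives the wrong answer if followed. A deliberate choice is possible, but the text does not say so, and 'or' equally admits severe neutropenia. An explicit exception would be the way to admit selected thrombocytopenic patients.

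**Conclusion.** The point holds. As printed, one adequate count meets the marrow criterion however low the other is, and this works against the requirement that opens the sentence. That 'and' was intended is an inference from the stated purpose, the other connectives and the role of the exemption; it is probable, not proven.

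The effect is on eligibility and safety at entry. The size in patients cannot be derived from the article. The primary analysis population is built from eligible patients who received at least one cycle, so the rule helps decide who is counted. The sample size, significance level, power and exact binomial test are unaffected. The conclusion concerns the published wording; whether the trial's operative rule has the same fault depends on the full protocol.

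**What to change.** Replace 'or' with 'and', so that both floors bind: neutrophils ≥ 0.75 × 10⁹/L and platelets ≥ 50 × 10⁹/L. Keep the infiltration exemption, and have the sponsor confirm from the full protocol whether it applies to platelets only or to both counts, then say so.

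The cost is one word and one check against the full protocol. If that document already says 'and', correct the article alone. If it also says 'or', sites need a clarification or amendment; since "Patient enrollment started in November 2019", it would apply only to patients still to be enrolled.

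The downside is that a few patients with one low count from a cause other than infiltration, such as hypersplenic or autoimmune thrombocytopenia, become ineligible. Whether to admit them through a stated exception is the sponsor's clinical decision.

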### Treatment

Patient enrollment started in November 2019. Eligible patients receive an induction phase of copanlisib and rituximab followed by a maintenance phase of each test drug (Fig. 2). The induction phase consists of six cycles (1 cycle = 28 days). Copanlisib will be administered intravenously at a fix dose of 60 mg on days 1, 8, 15 of each cycle. Rituximab will be applied intravenously at a dose of 375 mg/m^2^ only on day 1 of each cycle.

**Fig. 2 Fig2:**
[figure not shown]
Trial design. i.v. = intravenous

Maintenance starts 2 months after the last induction cycle for patients at least achieving a stable disease after induction. During maintenance time copanlisib is administered at a dose of 60 mg on days 1 and 15 every 4 weeks for a maximum of 12 cycles. Rituximab application is scheduled at a dose of 375 mg/m^2^ every 8 weeks for a maximum of 12 infusions unless progression or study drug-related intolerable toxicity. In the follow-up phase, all subjects who enter the trial will continue to be followed every 3 months for disease progression, subsequent treatment and survival for 2 years after completion*/*discontinuation of treatment. Subsequently, patients will be monitored every 6 months for three additional years.

### Study objectives

The objective of the trial is to test the efficacy and toxicity of treatment with copanlisib and rituximab in patients with MZL in need of treatment, who have failed, are not eligible for local therapy or relapsed. The primary end point of this study is the CR rate determined 12 months after start of induction therapy. For efficacy the rate of complete remissions according to the GELA criteria for gastric MZL or to the Cheson 2007 criteria for non-gastric extranodal, nodal and splenic MZL will be primarily analysed. Secondary efficacy end points include response rates (CR, PR and OR [CR or PR]), best response, time to best response, time to first response, progression-free survival, time-to-treatment failure, remission duration, cause specific survival and overall survival. Quality of life assessment, based on the functional assessment of cancer therapy for lymphoma version 4 (FACTLym) will be measured before start of treatment, during induction and maintenance.

